##### Secondary outcome analyses

We will analyse continuous secondary outcomes measured at baseline and follow-up for both groups in a similar way as the primary outcome. For categorical secondary outcomes (e.g. EULAR response categories, medication use), we will use mixed-effects logistic models. Since we wish to estimate the conditional, rather than the marginal, odds ratio of the outcomes, we will not include baseline values as model predictors for these models [63]. We will report effect estimates as 95% confidence intervals and consider intervals excluding a null effect as statistically significant. Results for the secondary outcomes will be reported both as estimates without adjustment to the type-I error level, as well as with Ryan–Holm step-down Bonferroni procedure-adjusted 95% confidence intervals [64] to account for multiplicity given the number of secondary outcomes.

For objective 4 (cost-effectiveness), we will undertake a health economic evaluation from a health system perspective with a sensitivity analysis from a societal perspective. For the health system perspective, we will take unit costs from relevant publicly available sources, such as the Unit Costs for Health and Social Care [65], National Cost Collection Data for NHS England [66] and the British National Formulary [67]. The societal perspective sensitivity analysis will include broader costs outside of the healthcare system, including work productivity and travel time as reported by patient trial participants. We will calculate the incremental cost per quality-adjusted life-year gained by multiplying resource use by appropriate unit costs, and utilities calculated from the EQ-5D-5L. We will develop a generalized linear mixed-effects regression model to estimate mean values and 95% percentiles using non-parametric bootstrapping.

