**Secondary objectives**				
2a	Treatment response categories	EULAR response categories [44]	Derived from DAS28-CRP	Difference in proportion of participants meeting good/moderate/non-response at t4 between control and intervention group^b^
	Patient-reported disease activity	RAPID-3 [45]	Patient web survey	Difference in RAPID-3 total score at t4 between control and intervention group^b^
		Patient global assessment	Patient web survey	Difference in patient global assessment score at t4 between control and intervention group ^b^
		RAID [46]	Patient web survey	Difference in RAID score at t4 between control and intervention group^b^
		CDAI [47]^c^	Patient web survey	Difference in CDAI score at t4 between control and intervention group^b^
	Joint involvement and severity	TJC28	EHR extraction	Difference in TJC28 score at t4 between control and intervention group^b^
		SJC28	EHR extraction	Difference in SJC28 score at t4 between control and intervention group^b^
	Medication use	n/a	EHR extraction	Difference in medication use of prescribed medication at t4 between control and intervention group^b, d^
	Work impairment	WPAI-RA [48, 49]	Patient web survey	Difference in WPAI-RA score at t4 between control and intervention group^b^
	Quality of life	EQ-5D-5L [50]	Patient web survey	Difference in EQ-5D-5L health profiles, index score and quality-adjusted life years at t4 between control and intervention group^b^
	Disability	HAQ [51]	Patient web survey	Difference in HAQ score at t4 between control and intervention group^b^
2b	Patients’ experience of shared decision-making during clinic visits	CollaboRATE [52]	Patient web survey	Difference in CollaboRATE score at t4 between control and intervention group^b^
	Researcher-observed shared decision-making processes during clinic visits	OPTION5 [53]	Clinic observations	Difference in OPTION score at t4 between control and intervention group^b^
	Patients’ experience of clinic visit quality	PEI [54]	Patient web survey	Difference in PEI score at t4 between control and intervention group^b^
	Patients’ self-management	COM-B [55]	Patient web survey	Difference in COM-B score at t4 between control and intervention group^b^
	Patients’ understanding of their RA	Brief IPQ [56]	Patient web survey	Difference in brief IPQ score at t4 between control and intervention group^b^

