*CDAI* Clinical Disease Activity Index for RA, *CollaboRATE* share decision making questionnaire, *COM-B* Capabilities, Opportunities, Motivations for Behaviour change questionnaire, *CRF* Case report form, *DAS28-CRP* Disease Activity Score for 28 joints using C-reactive protein, *EHR* Electronic health record, *EULAR* European Alliance of Associations for Rheumatology, *EQ-5D-5L* EuroQol five-dimension scale questionnaire, *HAQ* Health Assessment Questionnaire, *IPQ* Illness Perception Questionnaire, *PEI* Patient Enablement Instrument, *RA* rheumatoid arthritis, *RAID* Rheumatoid Arthritis Impact of Disease score, *RAPID-3* Routine Assessment of Patient Index Data 3, *SJC28* Swollen Joint Count for 28 joints, *TJC28* Tender Joint Count for 28 joints, *WPAI-RA* Work Productivity and Activity Impairment questionnaire: Rheumatoid Arthritis

^a^For remote consultations, we collected a CDAI score [47] instead of a DAS28 as calculation of the former does not require a blood test

^b^After accounting for measured variables that improve estimate precision, including cluster and outcome assessment at t0 (i.e. baseline); t4 is the time of final follow-up at 12 ± 3 months

^c^Our PPIE group developed a ‘Checking your tender and swollen joints’ section on the study’s website [38] with instructions and a training video for patients on how to self-assess and count tender and swollen joints

^d^Medication use at baseline includes past (i.e. previous 6 months) and current exposures, with any changes to RA medication recorded at all subsequent follow-up visits

^e^Includes number and dates of in-person rheumatology consultations and related travel time/costs, telephone rheumatology consultations, general practitioner consultations and hospital admissions

^f^Related to in-person rheumatology outpatients visits

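### The reason given for leaving baseline values out of the logistic models is reversed, and it contradicts Table 1 footnote b, most clearly for medication use

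*Protocol article*

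**What the plan says.** Three places in the protocol article bear on this.

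- **Secondary outcome analyses** (Statistical methods). The outcomes concerned are introduced as "For categorical secondary outcomes (e.g. EULAR response categories, medication use" and so on, and for them "we will use mixed-effects logistic models". The next sentence gives the reason for the covariate choice: "Since we wish to estimate the conditional, rather than the marginal, odds ratio of the outcomes, we will not include baseline values".
- **Table 1, objective 2a.** The metric for EULAR response is "Difference in proportion of participants meeting good/moderate/non-response at t4 between control and intervention group". Medication use is also given as a between-group difference at t4. Both rows carry footnote b, and medication use carries footnote d as well.
- **Table 1 footnotes.** Footnote b reads "After accounting for measured variables that improve estimate precision, including cluster and outcome assessment at t0 (i.e. baseline" (the closing bracket follows). Footnote d says "Medication use at baseline includes past (i.e. previous 6 months) and current exposures".

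For contrast, the primary model includes baseline DAS28-CRP, and continuous secondary outcomes measured at baseline and follow-up are to be analysed in a similar way.

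**The concern.** An odds ratio is conditional on whatever is in the model. It is also non-collapsible: averaging over a prognostic covariate changes its value even when that covariate is perfectly balanced between groups. A plan that wants the odds ratio conditional on baseline must therefore include baseline. This plan names the conditional odds ratio as its target and gives that as the reason for omitting baseline, so model and stated estimand point in opposite directions.

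Footnote b says the reverse about covariates for the same two outcomes. An analyst cannot follow both places, and the two choices give different numbers with different meanings. At stake are the correct label for the estimate, its comparability with other reports, and some power in secondary analyses that also face a step-down multiplicity adjustment.

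**Working it through.** The section states no figure for these outcomes, so there is none to reproduce. The check has a comparison of the text and an illustration of size.

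**1. The text side by side**

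| Outcome | Secondary outcome analyses | Table 1 footnote b | Baseline value available? |
|---|---|---|---|
| Medication use | baseline not a predictor | t0 assessment accounted for | Yes, footnote d: direct conflict |
| EULAR response | baseline not a predictor | t0 assessment accounted for | No category at t0; it is derived from DAS28-CRP, which is measured at t0 |

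**2. Continuous baseline covariate (all values assumed)**

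Model: logit P = log(OR)·trt + b·x, with x ~ N(0,1) and intercept 0, so the control proportion is 0.5. Averaging over x gives p₁ = E[expit(log OR + b·x)], and the odds ratio without baseline is p₁/(1 − p₁). For a conditional OR of 2.0:

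| b (logits per SD) | p₁ | OR without baseline | log-OR smaller by |
|---|---|---|---|
| 0 | 0.667 | 2.00 | 0% |
| 0.5 | 0.658 | 1.93 | 5% |
| 1 | 0.640 | 1.78 | 17% |
| 1.5 | 0.620 | 1.63 | 29% |
| 2 | 0.604 | 1.52 | 39% |

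Over b = 0.5 to 2, a conditional OR of 1.5 becomes 1.47 to 1.28 and one of 3.0 becomes 2.83 to 1.95. Control proportions of 0.3 and 0.7 give nearly the same values.

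**3. Binary baseline medication use (assumed)**

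Half the patients use the drug at baseline, and baseline use carries a log-odds g for later use. The conditional OR is 2.0, there is no clustering, and N = 432 (the planned analysis size). Then p₁ = ½[expit(−g/2 + log 2) + expit(g/2 + log 2)]. For g = 2, p₁ = ½(0.424 + 0.845) = 0.634, so the OR is 0.634/0.366 = 1.73. Expected z uses the large-sample standard error from each model's information matrix.

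| Baseline-use OR (e^g) | OR without baseline | Expected z, without baseline | Expected z, with baseline |
|---|---|---|---|
| about 3 (g = 1) | 1.92 | 3.30 | 3.39 |
| about 7 (g = 2) | 1.73 | 2.81 | 3.12 |
| about 20 (g = 3) | 1.53 | 2.17 | 2.73 |

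**4. EULAR-type good response (simulated, assumed)**

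The effect of 0.6 and follow-up SD of 1.2 come from the sample size section. Everything else is assumed: baseline mean 4.8 and SD 0.96, control mean 3.9 at follow-up, and good response taken as a fall above 1.2 to a score of at most 3.2. There is no clustering. With baseline-to-follow-up correlations of 0.3, 0.5 and 0.7, the odds ratio without versus with baseline is 2.34 v 2.38, 2.48 v 2.60 and 2.80 v 3.22. Other dichotomies of the score ranged from 3.06 v 3.11 to 2.27 v 3.32.

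**5. Does the cluster random effect rescue the word conditional?**

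On the latent logistic scale an ICC of 0.05 (the value planned for the primary outcome) corresponds to a cluster variance of (0.05/0.95)·π²/3 = 0.173. Averaging over cluster alone moves an OR of 2.0 to 1.95. The model conditions on cluster with or without baseline, so this cannot be the reason to omit baseline.

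**The case against.** The strongest defence has four parts.

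- **The odds ratio remains conditional in some sense.** A mixed-effects logistic model conditions on cluster, and the section excludes only baseline values, not other covariates. This stands. A reader might infer that the plan reports an unadjusted odds ratio, but the text does not say so. The accurate description is: not conditional on baseline.
- **A marginal odds ratio is a legitimate target.** The two terms may simply have been swapped, and the primary outcome is itself framed as a marginal mean. That is possible, and the analysis would then be coherent once relabelled. Footnote b would still be wrong.
- **EULAR response is a weaker case.** Footnote b is attached to most quantitative rows of Table 1 and cannot apply literally to a category with no t0 value. This stands, so the explicit contradiction rests on medication use.
- **Detail is deferred.** The section calls itself a summary and leaves specifics to the full statistical analysis plan. That excuses omissions, but not a stated reason that is the reverse of the truth.

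A reader might also argue that omitting baseline is dangerous because only 16 clusters are randomised and sites may learn the arm. The documents do not support a claim of that strength. Every cluster recruits to both conditions, switch times are not disclosed to sites, patients learn their allocation on consenting, and no size of imbalance can be derived.

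**Conclusion.** The point holds in this form: the stated rationale is reversed, and it conflicts with Table 1 footnote b, explicitly so for medication use. Followed as written, the plan would report an odds ratio averaged over baseline under the label of a conditional one.

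It should not be read as saying that the estimate will certainly be attenuated. That requires a prognostic baseline and a true odds ratio other than 1. Nor does non-collapsibility invalidate the test of no effect; the costs are the wrong label and some power. The sizes rest entirely on assumed baseline associations: a log odds ratio 5% to 39% smaller over 0.5 to 2 logits per SD, and possibly very little for EULAR response. The primary and continuous secondary analyses are unaffected. The error is definite, confined to categorical secondary outcomes, and worth correcting before the analysis plan is final.

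**What to change.** Preferred: delete the sentence, and include baseline medication use in the medication model and baseline DAS28-CRP in the EULAR response model. This agrees with footnote b and with the handling of continuous outcomes, and it makes the word conditional correct.

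Alternative: if omitting baseline is deliberate, describe the odds ratio as not conditional on baseline (averaged over it, within cluster) and amend footnote b for these rows.

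Under either route, reconcile Table 1's difference in proportions for EULAR response with the odds ratio, for example by also reporting a standardised risk difference from the fitted model.

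The cost is a sentence or two in the statistical analysis plan, which is to be published before data lock, and a little extra code. Both baseline variables are already collected.

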#### Methods for interim and additional analyses

Since we are expecting engagement with integrated symptom tracking to vary between patient participants in the integrated symptom tracking group, we will conduct and report sensitivity analyses for ‘best-case’ and ‘worst-case’ scenarios, i.e. assuming very high and very low engagement across participants, respectively.

There are no formal interim or subgroup analyses planned.

#### Methods in analysis to handle protocol non-adherence and any statistical methods to handle missing data

We have developed processes and materials to minimize non-adherence and missing data (see ‘Strategies to improve intervention uptake and adherence (i.e. intervention fidelity)’). Where missing data exists, we will summarize and report missingness in terms of outcome, data source (e.g. eCRF, patient web survey) and reasons for missingness (e.g. participant loss-to-follow-up, withdrawal, protocol deviation).

For the primary outcome analysis, we will use multiple imputation by chained equations where data points are assumed to be missing at random. We will detail multiple imputation model specifications in the full statistical analysis plan, but in general, we will seek to impute across all variables included in the primary and secondary analyses; particularly since we expect the primary outcome (DAS28-CRP) to correlate strongly with other, secondary measures of disease severity (e.g. clinical disease activity index [47]).

A sensitivity analysis will replicate the primary outcome analysis using complete case analysis (i.e. using only observed data from the non-imputed final dataset) and we will present its findings alongside those from the primary outcome analysis. Should the study team feel that data may not be missing not at random (e.g. because of unanticipated events), we will revise the statistical analysis plan to include additional analysis strategies for quantifying the robustness of the point estimate generated from the primary analysis model. Any additional sensitivity analyses will be presented in the main REMORA2 trial report.

#### Plans to give access to the full protocol, participant-level data and statistical code

We intent to make the full (‘operational’) REMORA2 trial protocol, statistical analysis code, statistical analysis plan and synthetic de-identified versions of the trial analysis dataset(s) publicly available in our trial repository [40]. Access to participant-level data for future, ancillary studies is only permissible on request to the trial’s co-principal investigators ([name] and [name]), and will be considered on a case-by-case basis (also see ‘Availability of data and materials’).

#### Analytical software

We are planning to undertake all quantitative analyses using the most recently validated version of R [68] or another appropriate validated statistical software package. We will stipulate the software and version in the relevant reports and publications. Code for analyses will be shared in our repository [40].

### Oversight and monitoring

#### Composition of the coordinating centre and trial steering committee

The coordinating centre is at the University of Manchester, where most of the study team is also based. There are three internal oversight groups. First, the REMORA2 programme management group comprises individuals responsible for the day-to-day management of the trial, as well as at least one member of the PPIE group. They meet monthly to monitor management of the programme, progress across workstreams, communications, trial outputs and future plans. Second, the REMORA2 trial management group, a subgroup of the programme management group, meets monthly to monitor all aspects of the conduct and progress of the trial, ensure protocol adherence and take appropriate action to ensure the quality of the research. Lastly, the scientific committee includes all study team members responsible for the scientific integrity of the trial, complemented with a PPIE group representative. This committee meets monthly to discuss methodological challenges (e.g. with data analysis), review preliminary findings, present recent advances in the field of integrated symptom tracking and provide oversight of publications in draft.

Furthermore, we have established the REMORA2 programme steering committee. It has external representation from an independent chairperson, one other independent expert, an independent statistician with stepped wedge trial expertise and one independent patient representative. It additionally has internal representation from the co-principal investigators and the programme manager. Other invitees may include a PPIE group member, study team members, a sponsor representative, or funder representatives, as needed. The committee meets at least twice annually.

Lastly, we have convened an independent expert group that meets once every 9–12 months to advise on future implementation and scalability of integrated symptom tracking beyond the REMORA2 trial. Membership includes representation of patient and professional organizations, commissioners, healthcare providers, digital health industry, academia and guideline and regulatory bodies.

#### Composition of the data monitoring committee, its role and reporting structure

The programme steering committee did not deem an independent data monitoring committee necessary for the REMORA2 trial. Instead, the committee has taken on this responsibility to review accruing data and monitor for reasons that may require trial discontinuation. As no interim analyses are planned, reasons for discontinuation will be unrelated to the primary analyses but may instead concern unlikely events, such as significant numbers of unanticipated serious safety events, or a high number of sites withdrawing.

#### Adverse event reporting and harms

The programme manager is notified (via a standard report form) by delegated cluster staff in case of any serious adverse events or any device deficiency that might have led to a serious adverse event if (a) suitable action has not been taken, or (b) intervention has not been made, or (c) circumstances have been less fortunate. We will follow-up all reported events to a satisfactory conclusion.

#### Frequency and plans for auditing trial conduct

We undertake on-site monitoring in line with our sponsor’s auditing requirements [69] using a risk-based strategy for data quality to ascertain the frequency and intensity of monitoring visits required. We will conduct additional monitoring as and when needed.

#### Plans for communicating important protocol amendments to relevant parties

The co-principal investigators review and approve any changes in research plans and activities. Where necessary, changes are submitted in writing to the research ethics committee, Medicines and Healthcare Products Regulatory Agency (MHRA) and local research and development teams at hospital sites for approval prior to enrolment into an amended protocol. The programme manager tracks the amendment history and coordinates dissemination to all participating hospital sites, members of the study team at the coordinating centre and other co-investigators. Amendments potentially impacting people’s appreciation of trial risks will also be shared with participants, alongside updating their informed consent if required.

### Dissemination plans

Upon completion of the study, members of the study team will analyse the data and produce and publish at least one final study report in a peer-reviewed journal; we do not intend to use professional writers. Further publications and conference abstracts will be published in consultation with the REMORA2 scientific committee and following authorization by the co-principal investigators, who will apply the International Committee of Medical Journal Authors guidance to confirm authorship eligibility. We inform participants of study findings via the regular newsletters.

## Discussion

Despite the ongoing digital transformation of healthcare services worldwide, the evidence for effectiveness and value for money to support the roll-out of digital health interventions remains scarce [70]. At the same time, the UK’s National Institute of Care Excellence evidence standards framework for digital health and care technologies [71] requires the highest-level evidence for active monitoring interventions, such as integrated symptom tracking, to be adopted into the NHS. The REMORA2 stepped wedge cluster randomized controlled trial addresses this by generating robust evidence about the comparative effectiveness and cost-effectiveness of integrated symptom tracking compared to standard of care in people living with RA. In addition, we are undertaking several parallel activities to prepare uptake of integrated symptom tracking beyond the trial. These include exploring influencing factors for behaviour change and implementation through the process evaluation; working with relevant regional and national stakeholders to ensure we learn transferrable lessons on integrating daily symptom tracking into the NHS to inform regional and national policy; and seeking regulatory approval of our integrated symptom tracking intervention as a medical device. Although the pathway for commissioning digital services in the NHS remains largely opaque, we hope that—by producing the required evidence coupled with the knowledge, materials and stakeholder support to facilitate implementation—we optimize the chances of integrated symptom tracking being adopted more widely if demonstrated (cost-)effective at the end of the trial.

Another parallel activity is the development of a governance framework and eConsent prototype. The aim is to enable future patients to provide consent from home for their symptom or other patient-generated health data to be used for the purpose of direct care, as well as for population health research. This acknowledges the added value of high-frequency, longitudinal patient-generated health data for addressing research questions that are important to patients but currently remain unanswered, such as ‘Which of these treatments is likely to work faster for me?’. Combining routinely collected electronic health record data on medication use with daily patient-reported symptoms, as we are doing in the REMORA2 trial, will create a powerful and unique dataset for comparative effectiveness research.

Integrated symptom tracking offers additional opportunities to change and improve healthcare services beyond those being evaluated within this trial. Although at present we intentionally restricted the scope to RA patients with active disease and to healthcare professionals only viewing the tracked symptom data during planned outpatient visits, others have started investigating using patient-generated symptom data to reduce clinic visit frequency for patients who are stable or in remission [26, 29, 31]. Integrated symptom tracking might also allow patients to be seen at times of need, or to receive ‘just in time’ supportive interventions, such as self-management advice when flaring. We hope that providing evidence for the benefits and cost-effectiveness of integrated symptom tracking at *planned* clinic visits will pave the way for scaling up this initial version into the NHS, thereby enabling further research and innovation for advancing services for people with long-term conditions to receive the best possible care at the right time.

